### Safety assessment

2.11

(1)Adverse events: All adverse events reported throughout the trial period will be noted and the prevalence rate of the adverse events will be calculated. The ratio of the participants showing adverse events between the groups will be calculated and analyzed using the Chi-square test or Fisher exact test.(2)Laboratory test results: The means and standard deviations of the laboratory test results will be presented and the changes from the baseline will be compared using paired *t* test or Wilcoxon signed-rank test.(3)Vital signs: The means and standard deviations of blood pressure and heart rates measured at each visit will be presented and the patterns of significant changes in each item from the initial treatment to completion will be compared using paired *t* test or Wilcoxon signed-rank test.

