### Study phase

2.3

During screening at the hospital, the eligibility of the participants will be adjudicated based on their medical history, medication history, results of blood and urine tests, vital signs, SCORAD index, and Hanifin and Rajka diagnostic criteria. Then the participants determined to be eligible for the trial will visit the hospital (visit 1) within 2 weeks after screening and will be randomly assigned to the treatment or the control group. After group allocation, various surveys including AD survey and physical examination will be conducted, and the participants will be administered with the investigational drug 3 times a day for 4 weeks. After 4 weeks, the participants will be asked to visit the hospital again (visit 2) and undertake the same surveys, examinations, and blood investigations as those at visit 1. For the next 4 weeks, all drugs will be withdrawn except Lacticare, a concomitant drug, and the participants will be asked to visit the hospital (visit 3) and undertake the same surveys and investigations. The specific schedules and types of examinations are summarized in Table 1.

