### Statistical analyses

2.9

Appropriate statistical tests will be performed according to the characteristic of the data, the number of associated variables and their correlations, and the state of distribution. Windows Strategic applications software will be used for analysis. At a significance level of 5% and power of 80%, 95% confidence interval will be reported for the differences in the results between the groups. Participants with results of at least 1 efficacy outcome after administration of the investigational drug after randomization will be included for efficacy assessment. In addition, all subjects who will receive the investigational drug at least once and visit the hospital will be included for the safety assessment. Chi-square test or Fisher exact test will be used for the discrete variables, and analysis of variance or Kruskal–Wallis test will be used for the continuous variables.

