### Safety and adverse events

2.14

If the participants experience adverse events during the trial, the investigators will record verified items, such as the date of onset, date of recovery, association with the investigational drugs, related measures and treatment, and results in the case report form according to the name and severity of the adverse events. Until recovery or stabilization from the adverse events or verification that the adverse events were caused by the investigational drugs or factors unrelated to the clinical trial, follow-up on the adverse events will be continued. Abnormal laboratory test results and abnormal vital signs that are determined to be clinically significant will be recorded as adverse events. For safety assessment, blood and urine tests will be conducted during the screening visit and visit 2 after administration of the investigational drugs, and any physically abnormal signs will be observed before and after drug administration. Furthermore, through visit 3 (1 month after the completion of drug administration), follow-up will be continued to detect any adverse events.

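### Section 2.11 names only paired tests of change over time for laboratory values, blood pressure and heart rate, and does not apply the between-group rules of section 2.9 to them, although the aim is safety compared with placebo

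*Protocol article*

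**What the plan says.** Section 2.11 (Safety assessment) has three items.

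- **Adverse events** get a between-group test: "The ratio of the participants showing adverse events between the groups will be calculated and analyzed using the Chi-square test or Fisher exact test".
- **Laboratory tests**: "The means and standard deviations of the laboratory test results will be presented and the changes from the baseline will be compared using paired" t or Wilcoxon signed-rank tests.
- **Blood pressure and heart rate**: "the patterns of significant changes in each item from the initial treatment to completion will be compared using paired" t or Wilcoxon signed-rank tests.

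No between-group test is named in the second and third items, and neither says whether the paired tests are run by arm or on both arms together.

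Section 2.9 (Statistical analyses) states general rules that are not limited to efficacy: "95% confidence interval will be reported for the differences in the results between the groups", and "analysis of variance or Kruskal–Wallis test will be used for the continuous variables".

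On timing, section 2.14 says "blood and urine tests will be conducted during the screening visit and visit 2 after administration of the investigational drugs". Section 2.3 says that at visit 2 participants "undertake the same surveys, examinations, and blood investigations as those at visit 1", and that visit 3 repeats the same surveys and investigations.

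**The concern.** The abstract, introduction and discussion all give the aim as efficacy and safety compared with placebo. A paired test of change from baseline does not address that aim. It combines any drug effect with whatever else shifts a measure over four weeks, such as visit effects or season, and the placebo arm is there to remove exactly that. Where the authors wanted a between-group test they named one: for adverse events in section 2.11, and for efficacy in section 2.10, where the paired test is an addition to the independent t test. For laboratory values and vital signs only the paired test is named.

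These measures matter in this trial by the protocol's own account. The introduction lists ephedra and licorice root among the SCRT ingredients, and section 2.2.3 excludes recent users of drugs containing either, as well as patients with uncontrolled hypertension. Reading paired results side by side could present a common time trend as an effect of SCRT, or let an opposing trend mask a real one.

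**Working it through.** **1. The stated tests side by side**

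| Data | Section | Between-group test named there | Paired test named there |
|---|---|---|---|
| Efficacy, change at week 4 | 2.10 | Independent t test; ANCOVA | Paired t, as an addition |
| Adverse events | 2.11 (1) | Chi-square or Fisher exact | None |
| Laboratory values | 2.11 (2) | None | Paired t or Wilcoxon signed-rank |
| Blood pressure, heart rate | 2.11 (3) | None | Paired t or Wilcoxon signed-rank |
| Continuous variables in general | 2.9 | ANOVA or Kruskal–Wallis; 95% CI for group differences | None |

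The plan gives no figure on this point to reproduce, so what follows is an illustration.

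**2. Inputs**

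- Participants per arm: 30 planned with 20% dropout (section 2.7), so 30 × 0.8 = 24.
- Significance level 5% (section 2.7). Sidedness is not stated; two-sided is assumed.
- Common shift over time: not in the documents. Assumed 0 to 0.5 SD of the change score, equal in both arms.
- No drug effect, independent arms, paired tests run by arm (also an assumption).

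**3. Formulas**

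With common shift δ in SD units and n = 24, let p be the chance that the paired t test is significant in one arm:

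p = P(|T| > 2.069), where T is noncentral t with 23 degrees of freedom and noncentrality δ√24.

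Then P(significant on SCRT, not on placebo) = p(1 − p), and P(exactly one arm significant) = 2p(1 − p).

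Example, δ = 0.4: noncentrality 0.4 × 4.899 = 1.96, p = 0.467, and p(1 − p) = 0.467 × 0.533 = 0.249.

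**4. Results, 24 per arm**

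| Shift (SD) | p | SCRT only, p(1 − p) | Exactly one arm, 2p(1 − p) |
|---|---|---|---|
| 0 | 0.050 | 4.8% | 9.5% |
| 0.1 | 0.076 | 7.0% | 14.0% |
| 0.2 | 0.156 | 13.1% | 26.3% |
| 0.3 | 0.291 | 20.6% | 41.3% |
| 0.4 | 0.467 | 24.9% | 49.8% |
| 0.5 | 0.650 | 22.7% | 45.5% |

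A simulation of 40,000 trials per setting agrees: SCRT only in 4.7%, 13.4%, 20.7% and 23.1% at 0, 0.2, 0.3 and 0.5 SD. With 30 per arm it gave 4.8%, 15.1%, 22.5% and 18.6%. The two-sample t test on change was significant in 4.7% to 5.1% throughout, because a common shift cancels in the difference between arms.

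**5. Visits with laboratory tests**

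Section 2.14 places blood and urine tests at screening and visit 2. Section 2.3 lists the laboratory tests at screening, and surveys and physical examination at visit 1, yet then refers to blood investigations at visit 1 that visit 2 repeats. Visit 1 may fall up to two weeks after screening (section 2.3). The text therefore leaves open whether the laboratory baseline is screening or visit 1, and whether visit 3 includes laboratory tests.

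**The case against.** The strongest reply is that section 2.9 already supplies the comparison. Its confidence intervals for group differences and its independent-group tests for continuous variables are not confined to efficacy, and the same paragraph defines the safety population. A reader might infer from section 2.11 alone that the placebo arm goes unused for these measures; with section 2.9 in view, the documents do not support that. What they support is that section 2.11, the specific section, names a different kind of test and does not say whether the general rule governs. If it does, two families of test apply to the same variables with no main one chosen.

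Second, section 2.14 records clinically significant laboratory and vital-sign abnormalities as adverse events, which are compared between arms. A reader might infer that drug effects on safety cannot be separated from time effects at all. That goes too far: only changes in these continuous measures that are not judged clinically significant escape the comparison. A modest mean rise in blood pressure or heart rate is an example.

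Third, the size depends on an assumed shift. The range 0.3 to 0.5 SD, which gives 41% to 50% for exactly one arm, lies where that quantity peaks, and half of it is placebo-only significance. The pattern that would mislead is SCRT only. It counts as an error only if someone reads discordant p-values as a drug effect, and the protocol states no such rule. Nor is the paired test always less sensitive: with a 0.5 SD drug effect and no time trend, its power at n = 24 is 65%, against 40% for an unadjusted two-sample t test. A real effect is hidden only if time pulls the other way.

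Fourth, one might argue that screening makes regression to the mean a sure source of false change. The support is thin: section 2.2.3 gives numeric laboratory limits only for TSH (on both sides) and for platelets in a specific setting, and no blood-pressure cut-off.

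Finally, sections 2.1 and 2.3 refer to Table 1 for the schedule. It is not visible in the text reviewed and may settle the visit question.

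**Conclusion.** The point holds in a limited form. For laboratory values, blood pressure and heart rate, section 2.11 fixes paired tests of change over time as the only named inference and leaves it unclear whether the between-group rules of section 2.9 apply. Paired tests do not answer the stated aim of safety compared with placebo.

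With no drug effect, 24 per arm and a common shift of 0 to 0.5 SD, the misleading pattern of significance on SCRT only arises in about 5% to 25% of trials per parameter, against about 5% for a between-group test. These figures rest on the assumed shift, two-sided 5% tests, independent arms and testing by arm. Section 2.11 does not state that last feature; pooling the arms would ignore allocation altogether. The gap is confined to changes not judged clinically significant.

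The wording of sections 2.3 and 2.14 conflicts on which visits have laboratory tests, subject to Table 1. This should be corrected, but it does not threaten the primary analysis.

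**What to change.** In section 2.11, make the main analysis for each laboratory test, blood pressure and heart rate the between-group difference in change from baseline: SCRT minus placebo, with 95% confidence interval, adjusted for the baseline value (ANCOVA, as section 2.10 already provides for efficacy). State that the paired tests are descriptive, say whether they are run by arm, and say that they are not evidence of a drug effect. Add a sentence saying how the general rules of section 2.9 relate to these variables.

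Reconcile sections 2.3 and 2.14 with Table 1 on which visits have blood and urine tests, and name the visit that serves as the laboratory baseline.

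Cost: a few sentences and a few extra tables. No new data are needed.

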### Data management

2.12

The investigators will record all data collected during this clinical trial in the case report form provided by the client, and the clinical trial manager will keep a copy of the case report form. When there are missing data, the investigators will leave a remark with proper explanation. While making changes to the case report form, the original record will be recognizable and the clinical trial manager making such changes should sign it with the date. All the above information will be stored and managed by the AD Research Center at Wonkwang University Korean Medical Hospital, Iksan. In observation of the Personal Information Protection Act, the names of the participants will be kept confidential and the participants will be denoted only by the numbers assigned. The participants will be informed that all the clinical trial data will be stored in a computer and will be kept strictly confidential. The signed written consent will be stored by the clinical trial manager.

### Monitoring

2.13

For the trial to be adherent to the Korea Good Clinical Practice and for the trial data to be acknowledged upon registration both domestically and internationally, a Contract Research Organization, a specialized institute for monitoring, will monitor the entire process of the trial to assure accuracy and reliability of the data and improve the quality of clinical research. To confirm completeness and clarity of the case record forms, the source document will be compared and reviewed with the case record forms in the presence of the investigators, and they should always cooperate with the client. The data recorded in the protocol that are basic items required by International Conference on Harmonization's Good Clinical Practices (ICH-GCP) will be consistent with the source document and should be reported accurately. Any dose and/or therapy modifications, adverse events, history of concomitant medications, intercurrent illnesses developed during the trial period, and reasons for withdrawals and dropouts will be monitored. The monitoring visit reports will be composed of a summary of the visit, narrative description, issues, and checklist results.

### Safety and adverse events

2.14

If the participants experience adverse events during the trial, the investigators will record verified items, such as the date of onset, date of recovery, association with the investigational drugs, related measures and treatment, and results in the case report form according to the name and severity of the adverse events. Until recovery or stabilization from the adverse events or verification that the adverse events were caused by the investigational drugs or factors unrelated to the clinical trial, follow-up on the adverse events will be continued. Abnormal laboratory test results and abnormal vital signs that are determined to be clinically significant will be recorded as adverse events. For safety assessment, blood and urine tests will be conducted during the screening visit and visit 2 after administration of the investigational drugs, and any physically abnormal signs will be observed before and after drug administration. Furthermore, through visit 3 (1 month after the completion of drug administration), follow-up will be continued to detect any adverse events.

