### Study design

2.1

This study was designed as an investigator-initiated, double-blind, randomized, placebo-controlled clinical trial to assess the efficacy and safety of SCRT in patients with AD and respiratory symptoms. A total of 60 participants will be divided into an SCRT group and a placebo group at a 1:1 ratio and the study drugs will be administered for 4 weeks. At weeks 4 and 8 of follow-up, the participants will visit the study institute and be assessed the efficacy and safety (including the onset of adverse events). Specific schedules and investigations are summarized in Table 1 and Figure 1. The protocol (version 1.1) follows standard protocol items: recommendation for interventional trials guideline.

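### Section 2.14 lets follow-up of an unresolved adverse event end once its cause is verified, even when the verified cause is the study drug

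*Protocol article*

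**What the plan says.** Three statements in section 2.14 (Safety and adverse events) bear on this point.

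- **The end rule.** The limit of follow-up is given as "Until recovery or stabilization from the adverse events or verification that the adverse events were caused by the investigational drugs"; in full, the last alternative reads "or verification that the adverse events were caused by the investigational drugs or factors unrelated to the clinical trial, follow-up on the adverse events will" continue. Verification of the cause, whether the drug or something outside the trial, thus stands beside recovery and stabilization as an end point.
- **The record.** For each event, "the investigators will record verified items, such as the date of onset, date of recovery, association with the investigational drugs" and further items including treatment given and results.
- **Later contact and tests.** The section says that "through visit 3 (1 month after the completion of drug administration), follow-up will be continued to detect any adverse events", and that "blood and urine tests will be conducted during the screening visit and visit 2 after administration of the investigational drugs".

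The aim in section 2.1 is "to assess the efficacy and safety of SCRT in patients with AD and respiratory symptoms". Section 2.11 plans to compare the proportion of participants with adverse events between groups by chi-square or Fisher exact test, and to summarise blood pressure and heart rate at each visit.

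**The concern.** An exit for events shown to have nothing to do with the trial has an obvious rationale. An exit for events shown to be caused by the study drug does not. For those events a safety assessment needs to know whether the reaction resolved, how long it took and whether it left anything behind. As written, establishing that SCRT caused an event is itself a reason that permits the site to stop following it.

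At stake are the protection of participants, who include children from age 7, and the completeness of outcome data for drug reactions. An event closed on attribution would enter the safety report with its cause known and its outcome unknown.

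**Working it through.** No arithmetic applies: the point turns on the logic of one sentence, and the plan gives no figure to reproduce for it.

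**Step 1. The rule as a condition.** Follow-up may end if the event has recovered, OR has stabilized, OR is verified as drug-caused, OR is verified as unrelated to the trial. Applied to the possible states:

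| Clinical state | Cause | May follow-up end? |
|---|---|---|
| Recovered | any | yes |
| Stabilized | any | yes |
| Neither | not verified | no |
| Neither | verified unrelated | yes |
| Neither | verified study drug | yes |

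The last row is the defect. The clinical state controls the end of follow-up only while the cause is unverified.

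**Step 2. Against the items recorded.** The sentence on recording lists recovery date, association with the drug, and results. For an event in the last row, the association is known, while the recovery date does not yet exist and the result is not yet known. Causality therefore serves both as an attribute to record and as a reason to stop before the other attributes can be completed.

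**Step 3. Is it repaired elsewhere?**
- *Visit 3 in 2.14.* Contact continues to about one month after the last dose, but for the stated purpose of detecting events. No duty is stated to follow a known event to its outcome.
- *Laboratory tests in 2.14.* Blood and urine tests are named at screening and visit 2 only. Clinically significant abnormal results count as adverse events. Such an event first seen at visit 2 has no repeat test assured by this section.
- *Section 2.3.* Surveys and investigations are repeated at visit 3. The text does not say whether this includes blood tests. Table 1 is not shown, so nothing is concluded from it.
- *Section 2.11.* Blood pressure and heart rate are measured at every visit, so an event visible in those signs would be seen again at visit 3 whatever the causality verdict.
- *Section 2.13.* Adverse events are among the items monitored, with nothing on how long each is followed.

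Visit 3 softens the problem for some events. Nothing in the article removes the last row of the table.

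**Step 4. Effect on the planned analysis.** The test in 2.11 counts participants with at least one event. A participant is counted once the event is recorded, whether or not it is followed to its end, so the comparison does not change.

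**The case against.** The case on the other side limits the point in several ways.

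- **Selective loss.** A reader might infer that outcomes would go missing selectively for drug-attributed events and so bias the safety profile. The full sentence does not support that: a verdict of unrelated cause ends follow-up just as well. The drug-caused branch is the one without a rationale, but it is not the only exit.
- **Contradiction.** A reader might infer that the section contradicts itself because a recovery date is mandatory. The list is introduced as examples of verified items, and an event closed at stabilization has no recovery date either. The items can stay open; that is as far as the text goes.
- **Every related event.** A reader might infer that follow-up ends as soon as the association item is filled in. The end rule asks for verification of the cause, and nothing equates that with a routine association rating, which blinded investigators (section 2.6) make without knowing the allocation. The exit may be reached rarely.
- **Participants leaving observation.** They still attend visit 3, where vital signs are measured. What may end early is follow-up of the event, not attendance.
- **Condensed text.** The article condenses protocol version 1.1, and the sentence may be a translation slip. But this is not a detail left to the fuller document: the article states the rule, and nothing in it corrects the rule.

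These objections narrow the claim. They leave the literal reading intact: verified drug causation is sufficient to end follow-up of an open, unstable event.

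**Conclusion.** The point holds as a badly fixed safety rule. Section 2.14 permits follow-up of an event that is neither recovered nor stable to end once its cause is verified, including when that cause is the study drug, and no other section of the article withdraws this.

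Its size cannot be given as a number. The article projects no event counts and does not say what verification requires or how often it would come before recovery or stabilization. The consequence is confined to participant protection and to the outcome data of individual events. The efficacy analysis and the between-group comparison of adverse event proportions are unaffected, and no claim of bias in that comparison is made.

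The conclusion assumes that sites would apply the sentence as written and that the full protocol carries the same wording. If the full protocol words the rule differently, the correction belongs in the article alone. The sponsor should correct the sentence, although it does not threaten the trial's primary result.

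**What to change.** Reconcile the follow-up sentence in 2.14 with the outcome items listed just before it. Attribution to the study drug should be a recorded attribute and not by itself a reason to end follow-up of an event that has neither recovered nor stabilized. The revised wording should also make clear that a known event still open at visit 3 has its status recorded there, since the present text speaks only of detecting events. How and how long individual events are managed is for the sponsor and investigators to settle; no schedule is proposed here.

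The cost is a one-sentence change and a clarifying phrase, checked against the full protocol, plus a few extra follow-up contacts for drug-attributed events that would otherwise have been closed. Sample size, visit structure and planned tests do not change.
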